## Methods/design

All procedures involved in this trial with human participants will be conducted in compliance with institutional ethical standards and the Helsinki Declaration. Ethical approval to conduct the trial has been granted by the Capital District Research Ethics Board (protocol CDHA-RS/2009-371) and the Annapolis Valley District Research Ethics Board (protocol #2009-005).

### Study Design

This is a two parallel group, four-site, single-blinded, randomized trial with group assignment stratified using the Stroke Prognosis Instrument II (SPI-II) [5]. Figure 1 illustrates the sequencing of the study protocol.

**Figure 1 F1:**
[figure not shown]
**Flow chart outlining the study protocol**.

### Setting

Four community-based cardiac rehabilitation programs, three located in one urban/suburban environment (Halifax, Nova Scotia, Canada) and one in a more rural setting (Kentville, Nova Scotia, Canada) have been selected at intervention sites based on recruitment potential, adherence to the national guidelines for hyperacute and acute management of NDS and TIA [60], and availability of existing programs that could be adapted to meet the protocol for this trial.

### Participants

#### Inclusion Criteria

Participants will include males and females, over 17 years of age, who are within 90 days of diagnosis of first probable or definite TIA (symptom resolution in less than 24 hours) or ischemic or hemorrhagic NDS (National Institutes of Health Stroke Scale less than 6) [63] for which medical attention was sought.

#### Exclusion Criteria

Potential participants will be excluded if they present with contraindications to exercise testing and training, in accordance with American College of Sports Medicine Guidelines (ACSM) [64] and/or are participating in another study that could potentially confound the outcomes of this trial.

#### Participant recruitment

Recruitment pamphlets approved by the Research Ethics Board and checklists outlining the inclusion/exclusion criteria will be distributed in emergency rooms, physicians' offices, stroke units, and outpatient stroke clinics. The neurologists or internists directing acute stroke services and emergency room physicians in the trial sites will be trained to identify patients who meet the selection criteria and will notify the PREVENT Trial site coordinator of potential research subjects. The site coordinators will also communicate directly with the recruitment locations twice weekly for potential participants and will provide ongoing education, recruitment flyers, and reminders about the trial. The site coordinators will also review each candidate's health record for inclusion/exclusion criteria and record basic demographic and medical information.

Eligible patients will be approached by the site coordinator, who will briefly explain the purpose of the study and ask if they have an interest in participating. If a potential participant expresses interest, the study will be explained in detail, all questions will be addressed and the participant will be asked to sign the consent form approved by the Research Ethics Board of that site. The family physicians of the participants will be informed of intent to participate. The Environmental Supports for Physical Activity Questionnaire [65] will also be administered. Those patients who do not wish to participate will be asked to complete a brief questionnaire about their daily physical activity, to assess the representativeness of the final study sample.

#### Sample Size

Systolic blood pressure, the most robust predictor of secondary vascular events [14], was selected as the outcome variable for sample size calculation. Using estimates obtained from our pilot study, a sample size of 119 in each group will have 80% power to detect a difference in means of 4.9 mmHg, assuming that the common standard deviation is 13.4 using a two group t-test with a 0.05 two-sided significance level. We have allowed for an overall attrition rate of 5% [55], thus increasing the sample size to 125 per group (250 in total). The trial will not be sufficiently powered to determine the effectiveness of the PREVENT intervention in reducing recurrent TIA, stroke or cardiac events. Thus, it will be exploratory in this regard and will help inform the design of a future, more extensive trial.

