There is good reason to suggest that risk factor management for NDS/TIA should be aligned with that of cardiovascular conditions, given that secondary risk factors, risk of recurrence, and the potential benefits of treatment are similar [2]. Preliminary support for a multi-faceted approach to secondary stroke prevention comes from a modeling study in which the authors concluded, ″At least four-fifths of recurrent vascular events in patients with cerebrovascular disease might be prevented by application of a comprehensive, multi-factorial approach″ [52]. A non-randomized study of a 3-month exercise program for patients within six months of NDS/TIA demonstrated improvements in walking endurance and exercise capacity [53]. Another non-randomized study of an 8-week educational program for people post-NDS/TIA demonstrated improved knowledge regarding stroke warning signs, medication adherence, blood pressure monitoring and reduction in salt intake [54]. A recent pilot randomized trial of a 10-week cardiac rehabilitation program for patients post-stroke demonstrated greater improvement in cardiac risk scores in the experimental group than the usual care group [55]. However, high-level evidence of risk factor reduction through non-pharmacological approaches is lacking [56]. For the most part, secondary stroke prevention trials have been short-term, focusing on pharmacological interventions (for example [57,58]) and endarterectomy for patient with surgical grade carotid stenosis [59].

Little provision is made in current health services for modification of lifestyle factors such as cardiovascular fitness, weight optimization and healthy eating for long-term secondary prevention in patients with NDS/TIA. This situation is at odds with recommendations supporting a combination of comprehensive lifestyle interventions and pharmacological therapy to prevent recurrent stroke and acute cardiac events in stroke survivors [60,61]. Indeed, Myint and colleagues [62] postulated that behavioral modifications may be as important as anti-hypertensive and cholesterol lowering agents in secondary prevention of stroke.

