A major thrust in public health over the next decade will be to focus attention on identification and management of vascular risk factors. Although primary prevention is the ultimate goal, resources will need to be allocated to those who are at high risk and most likely to gain the greatest benefit. One such group is people who have experienced a NDS/TIA. The main objective of the PREVENT trial is to determine whether the timely delivery of a comprehensive program of secondary stroke prevention services and coordinated care can improve long-term vascular risk reduction for patients after NDS or TIA. The primary aim is to compare the effectiveness of a program of rehabilitative exercise and education (PREVENT) versus usual care (USUAL CARE) in reducing vascular risk factors in people who have had a NDS or TIA. Secondary aims are to compare between PREVENT and USUAL CARE groups (i) exercise capacity, walking endurance, daily physical activity, number of cigarettes smoked daily, medication adherence; (ii) fatigue, cognitive function, depression, health-related goal attainment and health-related quality of life; (iii) direct health costs incurred over a 1-year period; (iv) reduction in secondary vascular events, within the limitations in sample size and trial duration. We anticipate that, in comparison to USUAL CARE, timely delivery of PREVENT will produce clinically important and sustainable improvements in the outcome variables.

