### Outcome Measurement

Given the long duration and multi-modal nature of the interventions, a range of outcome measures will be used to ensure evaluation of relevant variables that span the domains of the International Classification of Functioning [66]. The variables and measurement tools that will be employed are summarized in Table 1. These measures were selected based on the primary and secondary aims of the trial, clinical relevance, psychometric qualities, and feasibility (availability, cost and administration time). Evaluations will be conducted over a 2-day assessment period at baseline, post-intervention, six months, and 12 months by trained assessors blinded to knowledge of study hypotheses and group assignment. At each assessment the assessors will be asked to record their 'guess' as to the group assignment of each participant.

**Table 1 T1:** Outcome variables, measurement tools and assessment schedule

Variable	Measurement tool	Baseline	Post-intervention	6-month follow-up	12-month follow-up
*Primary measures*					

Blood pressure	Sphygmomanometer [67]	√	√	√	√

Waist girth	Tape measure [68]	√	√	√	√

Lipid profile*	Biochemical analysis	√	√	√	√

Fasting serum glucose	Biochemical analysis	√	√	√	√

Haemoglobin A1c	Biochemical analysis	√	√	√	√

*Secondary measures*					

Aerobic fitness	Peak VO_2 _using maximal treadmill stress test (ramp protocol)	√	√		√

Lower extremity function	Short Physical Performance Test [69]	√	√	√	√

Walking endurance	Six-Minute Walk Test [70]	√	√	√	√

Physical activity	Step Watch™accelerometers	√	√		√

	International Physical Activity Questionnaire [71]	√	√	√	√

Fatigue levels	Fatigue Assessment Scale [72]	√	√	√	√

Cognition	Montreal Cognitive Assessment [73]	√			√

Mental health	Hospital Anxiety and Depression Scale [74]	√	√	√	√

Quality of sleep	Pittsburg Sleep Quality Index [75]	√	√	√	√

Tobacco use	Self-report, using a health passport	√	√	√	√

Health care utilization	Self-report, using a health passport	√	√	√	√

Medication adherence	Self-report, using a health passport	√	√	√	√

Health-related quality of life	Medical Outcomes Study Short-form 36-item Questionnaire [76]	√	√		√

Health-related goals	Goal Attainment Scaling [77]	√	√	√	√

Secondary vascular events**	Health record abstraction	√	√	√	√

*Includes total cholesterol, high-density lipoprotein cholesterol (HDL-C), low-density lipoprotein cholesterol (LDL-C), triglycerides

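### The 5% attrition allowance rests on a pilot of a 10-week programme and is not shown to cover the 12-month follow-up, and the sample size has no reserve beyond it

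*Protocol article*

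**What the plan says.** The protocol article sizes the trial on systolic blood pressure: "Systolic blood pressure, the most robust predictor of secondary vascular events [14], was selected as the outcome variable for sample size calculation". Under Sample Size it states that "a sample size of 119 in each group will have 80% power". The target is a 4.9 mmHg difference between groups, the SD is taken as 13.4 in both, and the test is a two-sided two-group t-test at 0.05. It then adds the allowance for loss: "We have allowed for an overall attrition rate of 5% [55], thus increasing the sample size to 125 per group (250 in total".

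Reference 55 is the only support cited for the 5%. The Background introduces that reference as "A recent pilot randomized trial of a 10-week cardiac rehabilitation program for patients post-stroke". It gives the length of the programme, but not the length of follow-up or the loss rate.

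The main objective, at the end of the Background, is to learn whether the programme "can improve long-term vascular risk reduction for patients after NDS or TIA". Outcome Measurement sets the schedule: "Evaluations will be conducted over a 2-day assessment period at baseline, post-intervention, six months, and 12 months". Table 1 has blood pressure measured at all four visits. The Sample Size section does not say to which visit the 80% power refers.

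**The concern.** Attrition accumulates with time. An allowance described as overall has to cover the whole period up to the visit that carries the conclusion. Here the objective is long-term, and the last visit, at 12 months, is where cumulative loss is greatest. The source is known to the reader only as a trial of a 10-week programme. If its loss rate was counted over a period of about that length, it says little about retention at one year.

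What is at stake is the power statement for the trial's main question. The randomised number was set so that 5% loss leaves almost exactly the number needed. Any greater loss at 12 months would take the stated t-test below 80%.

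**Working it through.** **Inputs from the protocol article, Sample Size:** difference Δ = 4.9 mmHg, common SD σ = 13.4, two-sided α = 0.05, 119 evaluable and 125 randomised per group, 5% attrition. **Assumed, because the document does not give them:** loss rates above 5%, and the correlation r between baseline and 12-month systolic pressure.

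**Step 1. Reproduce the stated sample size.** The standardised difference is Δ/σ = 4.9/13.4 = 0.3657. Power of the two-group t-test with n per group comes from the noncentral t distribution with 2n − 2 degrees of freedom and noncentrality 0.3657 × √(n/2).
- The n that gives 80% power is 118.4, rounded up to 119. This matches the plan.
- At n = 119 the noncentrality is 0.3657 × √59.5 = 2.82, and power is 80.2%.

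**Step 2. Reproduce the allowance.** 125 × 0.95 = 118.75 evaluable per group, with power 80.1%. The stated 80% is met at exactly 5% loss.

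**Step 3. Find the reserve.** The loss at which 125 falls to 118.4 is 1 − 118.4/125 = 5.3%. Nothing is left beyond that.

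**Step 4. Vary the loss rate d, with n = 125 × (1 − d) and the stated t-test:**

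| Loss d | Evaluable per group | Power for 4.9 mmHg | Difference detectable at 80% power |
|---|---|---|---|
| 5% (plan) | 118.75 | 80.1% | 4.9 mmHg |
| 10% (assumed) | 112.5 | 78.0% | 5.0 mmHg |
| 15% (assumed) | 106.25 | 75.6% | 5.2 mmHg |
| 20% (assumed) | 100 | 73.0% | 5.3 mmHg |

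For scale, keeping 119 evaluable by enrolment alone would need 119/(1 − d) randomised per group: 133 at 10%, 140 at 15% and 149 at 20%.

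**Step 5. See what baseline adjustment could recover.** If 13.4 is the SD of a single visit, adjusting for baseline reduces the residual SD to 13.4 × √(1 − r²). At 20% loss (100 per group):

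| Assumed r | Residual SD | Power at 20% loss |
|---|---|---|
| 0.3 | 12.8 | 77% |
| 0.4 | 12.3 | 80% |
| 0.5 | 11.6 | 84% |

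If 13.4 is instead the SD of change from baseline, this table does not apply. The document does not say which it is.

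**The case against.** The strongest reply has four parts.

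**The document shows no shortfall.** A reader might infer that the 80% is unlikely to hold at 12 months. The document does not support that: it gives no 12-month loss rate, and every rate above 5% used here is an assumption. It gives the programme length in reference 55 but not the follow-up. This trial itself has a 12-week programme and a 12-month follow-up, so programme length alone does not settle over what period loss was counted. This part stands, and it limits the point to missing support.

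**Vascular events are not attrition.** The Background quotes risks of secondary stroke or death of 10%, 19% and 31% by risk group, and it is tempting to read these as implying more than 5% loss. No time horizon is attached to them, and a patient with a further stroke can still have blood pressure measured. This stands too.

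**The planned analysis is not a 12-month t-test.** Data management and analysis specifies a repeated-measures mixed model on an intention-to-treat basis, and depending on how it is fitted, patients lost late may still contribute. This stands in part. The 80% is nevertheless claimed for a t-test, with no gain from the model claimed. The same section adds covariates only where groups differ significantly at baseline, so routine adjustment for baseline systolic pressure is not planned.

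**The arithmetic is right.** A reader might object that 119/0.95 = 125.3 calls for 126 per group, whereas 125 matches 119 × 1.05. The difference has no consequence, because 125 per group with 5% loss still gives 80.1%. It is not an error worth correcting.

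**Conclusion.** The concern holds as a gap in justification. The 5% is supported only by a pilot of a 10-week programme, and the document does not show that it applies to the 12-month follow-up on which the long-term objective depends. The calculation reproduces and is correct at its own assumptions, but the reserve ends at about 5% loss.

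The size is modest at 10% loss (about 2 percentage points of power) and more noticeable at 15% and 20% (about 4.5 and 7 points), on the stated unadjusted t-test with Δ = 4.9 and SD = 13.4. Treating 12 months as the deciding visit is an inference from the long-term objective and the schedule, because the Sample Size section names no visit.

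Two stronger conclusions should not be drawn. One is that the trial is underpowered, which would need a loss rate that the document does not contain. The other, in the opposite direction, is that baseline adjustment guarantees 80%: at 20% loss this requires r of about 0.4 or more and 13.4 to be a single-visit SD.

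**What to change.** Keep 250 patients and change the text as follows.

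1. In Sample Size, state that the power refers to systolic pressure at the 12-month visit, and give it over 5-20% loss: 80% falling to 73% unadjusted, with the detectable difference rising from 4.9 to about 5.3 mmHg.
2. Support the allowance with retention data from a source with 12-month follow-up, or with this trial's own retention, pooled over both groups and blinded. The trial is enrolling, so the latter can become available.
3. In Data management and analysis, prespecify baseline systolic pressure as a covariate in its analysis whether or not the groups differ at baseline. This would replace, for this outcome, the rule that depends on baseline significance tests. The measurement is already collected.
4. State whether 13.4 is a single-visit SD. If it is, give the adjusted power as conditional on the correlation (at 20% loss about 77%, 80% and 84% for r = 0.3, 0.4 and 0.5), not as an assurance that 80% is kept.

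The cost is a rewritten sample-size paragraph, one changed sentence in the analysis section, and a slightly less favourable stated power. No extra patients or visits are needed.

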#### Randomization Procedures

Participants will be randomized to one of two interventions: USUAL CARE or PREVENT. To ensure comparable groups in terms of neurological status, group assignment will be stratified using the SPI-II, which assesses long-term risk of stroke post-TIA or NDS using a 15-point scale [5]. Two strata will be used: 1. SPI-II Level 1 (0-3 points; low-risk), 2. SPI-II Level 2 (4-7 points; moderate-risk), and Level 3 (8-15 points; high-risk). An individual not associated with the study will use a computerized random number generator to randomly assign subjects to group. Allocation concealment will be ensured by using opaque, a sealed envelope containing group assignment, which will be revealed, in the presence of the participant, after completion of the baseline assessment. The participants (who are necessarily unblinded) will be requested to avoid informing blinded evaluators of their group assignment.

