**Methods/Design:**

A single blind, randomized controlled trial will be conducted at two sites to compare the effectiveness of a program of rehabilitative exercise and education versus usual care in modifying vascular risk factors in adults after NDS/TIA. 250 adults within 90 days of being diagnosed with NDS/TIA will be randomly allocated to a 12-week program of exercise and education (PREVENT) or to an outpatient clinic assessment and discussion of secondary prevention recommendations with return clinic visits as indicated (USUAL CARE). Primary outcome measures will include blood pressure, waist circumference, 12-hour fasting lipid profile, and 12-hour fasting glucose/hemoglobin A1c. Secondary measures will include exercise capacity, walking endurance, physical activity, cognitive function, depression, goal attainment and health-related quality of life. Outcome assessment will be conducted at baseline, post-intervention, and 6- and 12-month follow-ups. Direct health care costs incurred over one year by PREVENT versus USUAL CARE participants will also be compared. Ethical approval for the trial has been obtained from the relevant Human Research Ethics Boards.

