### Data management and analysis

Data collected at each site will be recorded on standardized forms and entered into a secure database using a centralized, web-based data entry system that contains quality control checks (e.g., range checks, notification of missing data). An independent Data Safety and Monitoring Board, consisting a cardiologist, neurologist and a statistician, has been set up to review mid-point results (or at any time that a serious adverse event occurs) and inform the investigators on issues of trial safety.

Descriptive statistics will be calculated for dependent and independent variables. Demographic and clinical characteristics of subjects in the experimental and control groups will be compared on admission using 2-sample t-tests (continuous data) and Chi-square analysis (nominal data). Nonparametric methods will be used when assumptions of normality are violated. Similar analyses will be used to compare characteristics of (i) patients who consent to participate versus those who do not; (ii) subjects who complete the study versus those who withdraw, in order to determine the representativeness of the sample. A mixed effects analysis of variance with repeated measures will be used to model the treatment effects for variables that are interval or ratio and conform to the assumptions of normality (i.e., BP, waist girth, total cholesterol, HDL-C, LDL-C, triglycerides, serum glucose, hemoglobin A1c, peak VO_2_, Six-Minute Walk Test, step counts). Non-parametric tests (Mann Whitney and Kruskall Wallis tests) will be used for ordinal level data (i.e., International Physical Activity Questionnaire, Fatigue Assessment Scale, Montreal Cognitive Assessment, Hospital Anxiety and Depression Scale, Pittsburg Sleep Quality Index, Goal Attainment Scaling) or where a normal data distribution is not found. To control for baseline differences between groups, variables that are significantly different at baseline will serve as covariates in the analyses. Data will be analyzed on an intention-to-treat basis. Significant omnibus effects will be probed with t-tests, using the Bonferroni correction to control for multiple comparisons. Multiple regression will be conducted where appropriate to examine relationships among variables. Software will include Access and SAS version 9.1. Alpha level will be < 0.05.

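### Allocation is stratified by SPI-II, but covariates are chosen by baseline significance, a test that a stratum balanced by design will almost never pass

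*Protocol article*

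**What the plan says.** Under Randomization Procedures, "group assignment will be stratified using the SPI-II, which assesses long-term risk of stroke post-TIA or NDS using a 15-point scale". There are two strata: SPI-II level 1 (0 to 3 points), and levels 2 and 3 together (4 to 15 points). The only reason given for stratifying is to make the groups comparable in neurological status. On the sequence itself the section says: "An individual not associated with the study will use a computerized random number generator to randomly assign subjects to group". Blocking is not mentioned, and SPI-II is the only stratification factor named, both here and under Study Design.

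Under Data management and analysis, the groups are compared at baseline with t-tests and chi-square tests, and then "variables that are significantly different at baseline will serve as covariates in the analyses". The interval and ratio outcomes, including blood pressure, go into a mixed effects repeated-measures analysis of variance, and significant omnibus effects are followed by t-tests. Ordinal outcomes, and outcomes that are not normally distributed, go to Mann-Whitney and Kruskal-Wallis tests. Neither the SPI-II stratum nor site is named as a model term.

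**The concern.** The two rules work against each other. Stratified randomisation exists to prevent a baseline difference in the stratifying factor, while the covariate rule admits a factor only if such a difference appears. The better the stratification works, the more surely the stratum is kept out of the model.

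When a prognostic factor has been balanced by design but is left out of a between-group comparison, its variance stays in the error term although it no longer contributes to the spread of the treatment estimate. The reported standard error is then larger than the true one, confidence intervals are wider than they need be, and the test rejects less often than its nominal 5%. What is at stake is precision that the design has already created and the analysis does not collect.

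**Working it through.** **Inputs from the article (Sample Size).** 119 per group, difference 4.9 mmHg, SD 13.4, two-group t-test, two-sided 0.05, 80% power; 250 randomised.

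**The plan's own figure.** SE of the difference = 13.4 × √(2/119) = 1.737, and 4.9/1.737 = 2.82. The exact noncentral t gives power of 79.9% at 118 per group and 80.2% at 119. The stated 119 is reproduced.

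**Can the stratum pass the baseline test?** Take 125 participants per stratum and blocks of 4. Each stratum can then be out of balance by only one participant. The worst table is 63 and 62 in one stratum against 62 and 63 in the other: chi-square = 250 × (63×63 − 62×62)² / 125⁴ = 250 × 125² / 125⁴ = 0.016, against a critical value of 3.84. A simulation of 3,000 trials of 250 with equal-probability strata agrees: the stratum was significant in 0.0% of trials with blocks of 4 or 8, and in about 5% with no blocking. Site, taken as four equal unstratified sites, was significant in about 5% either way, which is chance.

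**What does leaving it out cost?** Let R² be the share of outcome variance explained by the stratum. The article gives no value, so a range is assumed. With blocked allocation and a between-group comparison of means:

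- ratio of unadjusted to adjusted SE = 1/√(1 − R²)
- true type I error of the unadjusted test = 2 × P(Z > 1.96 × ratio)
- adjusted SE = 1.737 × √(1 − R²), from which adjusted power follows by the noncentral t

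| Assumed R² | SE ratio | True type I error, unadjusted | Adjusted SE | Adjusted power (80.2% as planned) |
|---|---|---|---|---|
| 0.01 | 1.005 | 4.9% | 1.728 | 80.6% |
| 0.02 | 1.010 | 4.8% | 1.720 | 81.0% |
| 0.05 | 1.026 | 4.4% | 1.693 | 82.2% |
| 0.10 | 1.054 | 3.9% | 1.648 | 84.2% |
| 0.20 | 1.118 | 2.8% | 1.554 | 88.1% |

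**Check by simulation** (238 analysed, blocks of 4, 6,000 trials per setting). At R² of 0.05, 0.10 and 0.20:

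- The unadjusted analysis reported SEs of 1.735, 1.736 and 1.737, while the estimate actually varied with SDs of 1.692, 1.657 and 1.548.
- Its type I error was 4.3%, 4.1% and 2.9%. Simulation error near 5% is √(0.05 × 0.95/6000) = 0.3 points.
- Power, unadjusted against adjusted, was 81.1% and 82.5%, 82.4% and 84.9%, 83.7% and 88.5%. Within the same stratified trial the gain from adjusting is therefore 1.4, 2.5 and 4.8 points.

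**Group-by-time test.** Baseline is one of the assessment times. A stratum shift that is constant over time cancels from each participant's change, so it does not sit in within-subject error. For that test only the share of variance in change explained by the stratum matters, and the figures above overstate the loss.

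**The case against.** Several points on the other side are sound.

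- *The article condenses a fuller plan, and its covariate sentence does not say that no other variable may enter.* True, and an unmentioned model term would be no finding. But selection by baseline significance is stated outright, and an analysis plan that carried it over would leave the stratum out. That stated rule is what is open to criticism.
- *The size is unknown.* SPI-II grades long-term stroke risk, not blood pressure, and the article gives no correlation with any primary outcome. R² could well be 0.02 or less, where nothing of practical weight is lost.
- *Blocking is not stated.* Without it, stratification achieves little and the unadjusted SE is valid. The rule would then admit the stratum about 5% of the time by chance, which is no better a reason for including it.
- *The main test may be group-by-time.* The article does not say which term is primary. However, the sample size rests on a two-group t-test and omnibus effects are probed with t-tests, so between-group comparisons are part of the plan.

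A reader might also infer that the benefit of stratifying is lost altogether, or that the trial is underpowered. The documents support neither. Comparable groups, the only stated aim, are achieved whatever the model. The sample size already uses the full SD of 13.4, and simulated unadjusted power stays above 80%.

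A reader might extend the argument to site. That fails too: site is not a stratification factor, so leaving it out neither contradicts the randomisation nor distorts the type I error.

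**Conclusion.** The point holds in a limited form. The article stratifies on SPI-II and then states a covariate rule that a balanced stratum will almost never meet (0% of simulated trials with blocking, about 5% without), so the analysis as written does not reflect the randomisation. The direction is conservative: no false-positive risk is created, and planned power is not undercut.

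The loss depends on three assumptions: blocked allocation within strata, a between-group comparison, and a stratum that predicts the outcome. Under these, at R² of 0.05 to 0.20, the standard error is 2.6% to 11.8% too large and about 1 to 5 points of power go unused. At R² of 0.02 or less, or for a within-subject group-by-time test, the effect is negligible or small. The change is worth making because it is nearly free, not because the trial is at risk without it.

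The number of sites is a separate matter. The abstract has "A single blind, randomized controlled trial will be conducted at two sites" and Study Design has "This is a two parallel group, four-site, single-blinded, randomized trial". Setting describes four programmes in two localities, so either count may be meant. The wording needs reconciling, but the article does not show which count is wrong.

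**What to change.** In Data management and analysis, replace the sentence that selects covariates by baseline significance. Suggested wording: *The parametric between-group (mixed) models will include the two-level SPI-II randomisation stratum as a fixed effect; covariates will not be selected by testing for baseline differences.*

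This costs one or two sentences and one degree of freedom (235 instead of 236 for a comparison of 238 participants). No new data are needed, because the stratum must be known before a participant can be allocated. The Mann-Whitney and Kruskal-Wallis tests take no covariates, so the change does not reach the outcomes analysed that way.

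Adjustment for site is optional. If it is wanted, site must first be defined for both arms: the four programmes are named as intervention sites, and the article does not show that usual-care participants are each linked to one of them. Reconcile the two-site and four-site wording as a separate edit.
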